### Additional outcomes

Adherence is measured using a self-constructed questionnaire, which has been used in a previous study by our research group [40], and contains 55 questions directed to support group therapists concerning the content of the support groups.

### Allocation

After completing the baseline assessment, participants are allocated to the intervention or the control group which represents care as usual (CAU). Due to the aforementioned reasons for abandoning the original randomization protocol, the vast majority of the control group participants are recruited from the support groups’ own waiting lists. Participants were informed about their group belonging by the project manager.

### The interventions

This study includes evaluating the effects of support groups in general that are aimed at children growing up in families with the above mentioned parental problems (*i.e.,* addiction to alcohol and/or other drugs, mental illness, domestic violence, divorce situation or imprisonment). Although these support groups are targeted at children with various underlying problems, they are all derived from the same fundamental manual-based intervention, Children are People Too (CAP) [26-28]. Depending on which programme/manual is being used, the design varies somewhat but generally consists of 8–15 group sessions (each between 90–120 minutes) discussing different aspects of parental problems in the family. Each session contains lectures related to the specific problem that the group aims at, and various games, role plays and practices related to family problem and coping behaviour [44,45]. Furthermore, every meeting focuses on a special theme and is structured in the same fashion, thereby making it recognisable from time to time to get children to feel more comfortable.

### The control

The control condition consists of a CAU waiting list. In Sweden, apart from support group interventions, usual care may involve support provided by for instance the social services (*e.g.,* contact families) and the school health care services, although it should be noted that this type of support is very uncommon. In severe cases children are referred to the Child and Adolescent Psychiatric Services.

### Sample size

This trial is designed to detect a medium or larger effect size corresponding to a standardized mean difference of Cohen’s d >0.5 [46]. Our hypothesis is directional in favour of the intervention. Based on differences between means, an *a priori* calculation of the estimated sample size, using the G*Power software [47] where an allocation ratio of 1.8 has been set, reveals that it is required that a minimum of 116 participants (75 in the intervention group and 41 in the control group) enrol in the trial (power = 0.80, α = 0.05, one tailed).

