### The target sample

The aim is to include at least 116 children, aged between 7 and 13 years at the point of enrolment, who intend and are eligible to participate in existing support group interventions targeted to children who grow up and live in families with at least one of the following parental problems: (1) addiction to alcohol and/or other drugs, (2) mental illness, (3) domestic violence, (4) divorce situation or (5) imprisonment. Participants will be excluded from the study if they do not meet the inclusion criteria, if they previously have participated in a support group intervention, or if they (or their parents) do not consent to participate.

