### Analyses

In addition to per protocol analysis, and if applicable, data will be analysed according to the intention-to-treat principle where all participants will be included irrespective of whether or not they have completed the intervention. Missing data will then be handled by multiple imputation using the Missing Value Analysis routine in the SPSS software (IBM SPSS Statistics 20, IBM Corporation).

The main analyses consist of comparing mean-values of outcome measurements between groups and within groups at the baseline and follow-up assessments. A follow-up at 12 months past the baseline is only conducted for the intervention group, precluding a between groups analysis at 12 months. Before analysis, all data will be merged and thus treated equally, irrespective of the nature of the support group (*i.e.,* parental problems related to for instance substance abuse, mental illness or domestic violence) that the child has participated in. Hence, the current design will not suffice analysis where data to a greater detail are differentiated based on the various support group interventions. Analyses include either parametric or non-parametric tests, depending on whether or not the various outcome data are normally distributed. The effects of the support group interventions will be estimated using Cohen’s convention of effect size [46].

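### The power of 0.80 is attached to 116 children enrolled, not to children with four-month data, and no allowance for loss is stated

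*Protocol article*

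**What the plan says.** The Sample size section of the protocol article sets out these inputs:

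- Effect: a "standardized mean difference of Cohen’s d >0.5".
- Direction: "Our hypothesis is directional in favour of the intervention".
- Error rates: "power = 0.80, α = 0.05, one tailed".
- Allocation: "an allocation ratio of 1.8 has been set".

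From these, G*Power is reported to require that "a minimum of 116 participants (75 in the intervention group and 41 in the control group) enrol in the trial". The target sample section repeats the figure as the inclusion goal: "The aim is to include at least 116 children".

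The Analyses section plans a per-protocol analysis and, where applicable, an intention-to-treat analysis. For the latter, "Missing data will then be handled by multiple imputation". The choice of test is left to the data: "Analyses include either parametric or non-parametric tests, depending on whether or not the various outcome data are normally distributed". Under Strengths and limitations, the article says that the groups can be compared with each other only at four months.

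No expected loss rate, inflation step or separate number of evaluable children appears in the article.

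**The concern.** A two-group power calculation returns the number of observations that enter the comparison. The article attaches that output, and the power of 0.80, to the number of children who enrol. The two coincide only if every enrolled child supplies four-month data.

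The plan does not expect that. A per-protocol analysis leaves out children who do not complete, and imputation is specified because outcomes will be missing. Imputation keeps those children in the intention-to-treat dataset, but it does not by itself restore the information lost with their outcomes.

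What is at stake is how a null result would be read. A reader would set it against a power of 0.80, when the power actually available may have been lower by an amount the article does not let the reader work out.

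**Working it through.** **Inputs.** All are from the Sample size section: d = 0.5 (SD = 1), one-sided α = 0.05, power 0.80, ratio 1.8, arms of 75 and 41. Loss rates are not in the article and are assumed here.

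**Formula.** For a two-sample t-test with n₁ and n₂ children with data:

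- degrees of freedom = n₁ + n₂ − 2
- noncentrality δ = d × √(n₁n₂ / (n₁ + n₂))
- power = P(noncentral t > t at 0.95)

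**Step 1: the plan's own figure.** At 75/41, δ = 0.5 × √(75 × 41 / 116) = 0.5 × √26.51 = 2.574. The critical value on 114 df is 1.658, and power is 0.820. The stated 0.80 is met if all 116 have data.

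**Step 2: how many the t-test needs.** At 71/39 (110 children), power is 0.802. At 70/39 (109), it is 0.79998, which is 0.80 only after rounding. So about 110 are needed, and 116 is six above that. The article does not explain the surplus or present it as an allowance for loss.

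**Step 3: proportional loss from 75/41, one-sided t-test.**

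| With data (intervention/control) | Total | Lost of 116 | δ | Power |
|---|---|---|---|---|
| 75/41 | 116 | 0% | 2.574 | 0.820 |
| 71/39 | 110 | 5.2% | 2.509 | 0.802 |
| 70/38 | 108 | 6.9% | 2.481 | 0.794 |
| 67/37 | 104 | 10.3% | 2.441 | 0.782 |
| 60/33 | 93 | 19.8% | 2.307 | 0.741 |

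With fractional children, the curve crosses 0.80 at 5.5% loss. In whole children, it is clearly below 0.80 at 108 (6.9%). Power is more than two points below 0.80 only once loss exceeds about 10.7%.

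**Step 4: unequal loss.** If all losses are controls, power falls below 0.80 at four children (75/37, power 0.796; 4/116 = 3.4%). If all are intervention children, it falls below at eleven (64/41, power 0.799; 11/116 = 9.5%).

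**Step 5: a rank test instead.** The article allows non-parametric tests. With a Wilcoxon-Mann-Whitney test and normally distributed data, the relative efficiency is 3/π = 0.955, and each arm is multiplied by this before the formula is applied. At 75/41, power is then 0.804; at 74/41 (115), it is 0.802. This matches 116 more closely than the t-test does. Under proportional loss, the crossing of 0.80 comes at about 1.1%.

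**The case against.** **The calculation is not wrong.** At 75/41 the stated power is met with a little to spare. This stands: the fault is in what the number is attached to, not in the arithmetic.

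**A reader might infer that 116 is exactly the number that must be analysed, so that any loss breaks the claim.** The article does not support that for a t-test, where about 110 suffice. It comes close to true only if 116 was derived for a rank test. The article does not say which test was used.

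**A reader might also infer that power collapses just past the threshold.** It does not. At 6.9% loss it is 0.794, and at about 10% it is 0.78. Differences of that size are within ordinary planning uncertainty for a conventional d of 0.5. A material drop needs loss nearer 20%, and the article gives no attrition figure to show that such loss is likely.

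**Retention is supported.** According to the Assessment section, project staff collect the four-month data, each completed assessment earns a gift card, and controls are offered the intervention after that follow-up. Postal collection at four months is an option for controls only, with telephone support. This is a fair reason not to presume heavy loss. It does not make loss zero.

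**The targets are floors, and an article condenses.** Wording that sets a minimum permits over-enrolment but does not plan it. A fuller protocol may hold an attrition assumption. Even so, the published sentence gives every input and then states the result as an enrolment count with power 0.80, and that sentence can be judged as it stands.

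**Conclusion.** The point holds in a limited form. The article presents 116 both as the calculated requirement and as the minimum to enrol, with no stated allowance for children without four-month data, although its analysis plan expects some.

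For the one-sided t-test at d = 0.5, the unexplained surplus covers proportional loss of about 6%. Beyond that, power is below 0.80: about 0.78 at 10% and 0.74 at 20%. If a rank test lies behind 116, the margin is about 1%.

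These figures assume the effect size and one-sided test that the article states, and loss that is proportional across arms and leaves the effect unchanged. For the rank test they also assume normally distributed data. The loss rates are illustrative. The shortfall is real but modest, and the sentence should be corrected; the design need not change.

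**What to change.** Make three changes to the Sample size section:

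1. Tie the power of 0.80 to children with four-month outcome data instead of children enrolled.
2. Name the test behind 116.
3. State the power expected from 116 enrolled under a stated loss. For example: with an assumed 20% loss, about 93 children are analysed (60 intervention, 33 control), giving power of about 0.74 for d = 0.5 with a one-tailed t-test.

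The sponsor should replace the 20% with its own expectation and recompute. The target sample section can keep 116 as its inclusion goal, provided that it is no longer read as the number that secures 0.80. The cost is a slightly less favourable published figure; no more children need to be enrolled.

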### Analyses

In addition to per protocol analysis, and if applicable, data will be analysed according to the intention-to-treat principle where all participants will be included irrespective of whether or not they have completed the intervention. Missing data will then be handled by multiple imputation using the Missing Value Analysis routine in the SPSS software (IBM SPSS Statistics 20, IBM Corporation).

The main analyses consist of comparing mean-values of outcome measurements between groups and within groups at the baseline and follow-up assessments. A follow-up at 12 months past the baseline is only conducted for the intervention group, precluding a between groups analysis at 12 months. Before analysis, all data will be merged and thus treated equally, irrespective of the nature of the support group (*i.e.,* parental problems related to for instance substance abuse, mental illness or domestic violence) that the child has participated in. Hence, the current design will not suffice analysis where data to a greater detail are differentiated based on the various support group interventions. Analyses include either parametric or non-parametric tests, depending on whether or not the various outcome data are normally distributed. The effects of the support group interventions will be estimated using Cohen’s convention of effect size [46].

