There are only a few estimates available reporting on the number of existing support groups in Sweden. Moreover, figures on how many children there are who attend support groups every year are even scarcer. According to a survey from 2009 by the Swedish National Institute of Public Health [29], support groups for children in families with parental substance abuse problems were available in 90% of all municipalities. For children affected by parental mental illness, the same figure was 73%, for children who have witnessed domestic violence the figure was 64% and 38% for children having a parent in prison. More recent surveys made by the Swedish Save the Children and the junior association of the Swedish IOGT-NTO (Junis) also show that the vast majority of municipalities provide support groups to children experiencing parental problems [30,31]. Yet, despite the fact that most municipalities do provide resources for support, only a small proportion of all children who live in troubled families attend this support. For instance, in an annual survey by Junis figures reveal that only 1-2% of all children who have parents with substance abuse problems attend support groups [31].

To our knowledge there are few controlled trials reported in the literature, measuring the effects of support groups with a theoretical basis in CAP. However, a few studies have been conducted using a quantitative approach, but without a control group. For instance, a Swedish effect study of 300 children aged 7–22 [26] was pursued without a control group, but using added value as the method of analyses [32,33]. Results revealed an improvement among the participants with regards to their mental health status, overall life satisfaction and hopefulness [26]. Results from another study using a small group of children who had attended a CAP-based support group after experiencing family violence, indicated an improved mental health status among the participating children [34]. Nonetheless, there is still a lack of evidence for CAP-based support groups and we have therefore designed a quasi-experimental controlled trial which evaluates the effectiveness of support group interventions targeted to children experiencing a wide variety of parental problems. Our hypothesis is that these support groups will render in positive effects among 7–13 year olds.

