### Objective and research questions

The objective of this study is to evaluate the effectiveness of support groups provided to children who grow up in families with parental problems (*i.e.,* addiction to alcohol and/or other drugs, mental illness, domestic violence, divorce situation or imprisonment). Specific research questions concerns the children’s improvement in mental health, coping behaviour and quality of life, which includes overall life satisfaction and future hope, self-perception and self-esteem, and emotional climate and personal interaction.

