## Methods/design

This study was originally designed as a two-armed randomized controlled trial (RCT). However, after several months of unsuccessful recruitment efforts, the randomization protocol was abandoned and the study redesigned as a quasi-experimental control group study (Figure 1). The reason for abandoning the RCT-design was the unwillingness of support group therapists to randomize participants into the control condition. This was due to the fact that support group therapists did not consider it ethically sound to randomly allocate children, who actively had sought support (by themselves or by their parents), into the control condition.

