### Assessment

Before being allocated to one of the two study conditions, participants have to complete the baseline measurement. All study participants also have to complete a follow-up assessment four months after the initial measurement. Additionally, the intervention group participants have to complete a second follow-up assessment 12 months after the initial measurement. This 12 month follow-up will only be available for the intervention group participants as the control group participants, for ethical reasons, will be offered the intervention after the four-month follow-up. All measurements are performed using paper-based questionnaires. The participants in the intervention group complete the initial baseline assessment during the first individual meeting, which precedes the first support group meeting. Baseline data from the interventions group is collected by the support group therapist responsible for the individual meeting, or by the project staff. Data from the four month follow-up assessments are collected by the project staff. For the 12 month follow-up (intervention group only), questionnaires are either distributed by regular mail (with telephone support available if needed) or in a meeting with the project staff (if requested by the child/parent). Data from the control group participants will be distributed and collected by the project staff in person or by using regular mail with telephone support if necessary. As a compensation for completing each assessment, children and parents are each given a gift card corresponding to approximately 22 or 11 Euro, respectively.

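### The analysis section gives uncontrolled before-after comparisons the same main status as the controlled contrast and does not say that the effect estimate is the between-group one

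*Protocol article*

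**What the plan says.** The Analyses section of the protocol article describes the main analyses as "comparing mean-values of outcome measurements between groups and within groups", at baseline and at follow-up. Both kinds of comparison stand in one sentence, with no ranking and no statement of which one decides effectiveness. The section continues: "The effects of the support group interventions will be estimated using" Cohen's convention, again without naming the contrast.

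On the long follow-up, the same section says: "A follow-up at 12 months past the baseline is only conducted for the intervention group, precluding a between groups analysis at 12 months". Under Assessment, "All study participants also have to complete a follow-up assessment four months after the initial measurement", so four months is the only controlled time point.

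The objectives are worded without a comparator: "Specific research questions concerns the children’s improvement in mental health, coping behaviour and quality of life". The opening of Methods/design describes the children as ones "who actively had sought support (by themselves or by their parents").

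Other parts of the article point to a controlled question. The Background notes that earlier evaluations had no control group and concludes: "Nonetheless, there is still a lack of evidence for CAP-based support groups". The Sample size section rests on a difference between group means. The Discussion presents the control group as the basis for judging effectiveness and as a strength of the study.

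**The concern.** A before-after mean change in one group combines any intervention effect with natural recovery, regression to the mean and the effect of repeated measurement. The earlier studies that the authors considered insufficient had this weakness. Making the same comparison a main analysis, and leaving the effect size untied, allows a before-after d to be reported as the effect of the support groups. The article does not mention natural improvement or regression to the mean; its limitations cover selection bias, mixed family problems and short follow-up.

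The unequal split adds to the problem. With 75 and 41 children, the same natural change is more likely to reach significance in the intervention group than in the controls, so two separate within-group tests can appear to show a contrast that does not exist.

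At stake is how the report could be read by the practitioners and policy-makers whom the article names as waiting for this evidence.

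**Working it through.** **1. The plan's own figure.** Inputs from the Sample size section: d = 0.5, one-sided alpha 0.05, power 0.80, ratio 1.8, and 75 + 41 = 116 children. For a two-sample t-test the noncentrality is 0.5 / sqrt(1/75 + 1/41) = 2.574 with 114 degrees of freedom. Power is 0.820, and the smallest sample reaching 0.80 is 39 + 71 = 110. With the Wilcoxon-Mann-Whitney option (efficiency 3/pi) the requirement is 41 + 74 = 115, and 75/41 has power 0.804. So 116 is reproduced closely by that option. It is a sample size for the between-group contrast only.

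**2. Assumptions not in the article.** No intervention effect; the same natural improvement g (in SD units) in both groups; baseline to follow-up correlation r of 0.5 to 0.7; complete data; one-sided 5% tests.

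The range for g can be related to regression to the mean, whose expected size is (1 - r) x baseline excess. An excess of 0.5 SD gives 0.15 to 0.25 SD for r from 0.7 to 0.5. An excess of 1 SD gives 0.3 to 0.5 SD.

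**3. Before-after test under no effect.** Paired t-test with noncentrality g / sqrt(2(1 - r)) x sqrt(n). For g = 0.2 and r = 0.6, g / sqrt(0.8) = 0.224. The noncentrality is 1.936 for n = 75 and 1.432 for n = 41, and the chances of significance are 0.608 and 0.406. The groups are independent, so the chance of a significant result in the intervention group only is 0.608 x (1 - 0.406) = 0.361. The reverse is 0.406 x (1 - 0.608) = 0.159.

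| g | r | Intervention (75) significant | Control (41) significant | Intervention only | Control only |
|---|---|---|---|---|---|
| 0 | any | 5% | 5% | 4.8% | 4.8% |
| 0.1 | 0.5 | 21.6% | 15.5% | 18.2% | 12.2% |
| 0.1 | 0.7 | 29.6% | 20.3% | 23.6% | 14.3% |
| 0.2 | 0.5 | 52.8% | 35.0% | 34.4% | 16.5% |
| 0.2 | 0.6 | 60.8% | 40.6% | 36.1% | 15.9% |
| 0.2 | 0.7 | 71.6% | 49.2% | 36.4% | 14.0% |
| 0.3 | 0.5 | 82.4% | 59.6% | 33.3% | 10.5% |
| 0.3 | 0.6 | 89.1% | 67.9% | 28.6% | 7.4% |
| 0.3 | 0.7 | 95.3% | 78.6% | 20.4% | 3.7% |
| 0.5 | 0.5 | 99.6% | 93.3% | 6.6% | 0.4% |
| 0.5 | 0.7 | over 99.9% | 99.2% | 0.8% | under 0.1% |

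**4. The between-group test under the same conditions.** In 20,000 simulated studies at r = 0.6 and g = 0.2 or 0.3, a between-group comparison of change scores or of follow-up scores was significant in 4.7% to 5.1%. This requires that the two groups share the same natural course.

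**5. How often the two comparisons disagree.** In 40,000 simulated studies at r = 0.6, the intervention-only pattern coincided with a significant between-group test in about 5% of all studies, at both g = 0.2 and g = 0.3. So of the 36% at g = 0.2, about 31% (36 - 5) come with a non-significant between-group result. Of the 29% at g = 0.3, about 24% (29 - 5) do.

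**The case against.** The strongest reply is that the article, read as a whole, is about a controlled comparison. The Discussion says effectiveness will be judged with two conditions, the sample size uses a between-group d, and the Analyses sentence names the between-group comparison first. That sentence could be a list of what will be computed. This stands in part: the intention is clear from other sections. But the Analyses section is where the ranking is fixed, and there the two comparisons are on a par.

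A reader might infer that the authors will claim success when the intervention group changes significantly and the controls do not. No section states such a rule. The 18% to 36% is therefore not the chance of a false conclusion. It becomes one only if a between-group result that is usually non-significant, and is also planned, is set aside.

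A reader might also infer that 12-month change will be presented as a long-term effect. The article does not support that. The Analyses section says no between-group analysis is possible then, and the limitations concede that firmer long-term evidence will not result. What is missing is only that this caveat governs the analysis section.

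The percentages depend on assumed values. The intervention-only pattern is highest around g = 0.2 to 0.3 and falls to 1% to 7% at g = 0.5, where both groups are nearly always significant. The article sets no symptom threshold for entry, so it does not show that children enter at a peak of difficulty. It shows only that support had been sought. Regression to the mean is plausible here, but its size is unknown.

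Finally, an unseen analysis plan may rank the comparisons. That would resolve the matter, but the published text has already given both main status.

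**Conclusion.** The point holds as a fault in what the Analyses section fixes: before-after comparisons share main status with the controlled contrast, and the effect size is not tied to the between-group difference. This conflicts with the study's own rationale and sample size.

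At a shared natural improvement of 0.1 to 0.3 SD and a correlation of 0.5 to 0.7, with no intervention effect, the intervention group's before-after test is positive in about 22% to 95% of studies. The between-group test is positive in about 5%. With no natural change both are at about 5%, so the size of the problem rests on values the article does not give. The direction does not: any natural improvement raises the error of the before-after test, while a natural course common to both groups leaves the between-group test at its nominal level. Because allocation is not randomized, that common course is itself an assumption.

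At four months the weakness is the equal status of the two comparisons, since a control group is available. At 12 months the article already concedes most of the point.

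**What to change.** In the Analyses section, name the between-group difference at four months, adjusted for baseline because allocation is not randomized, as the only main analysis and the only basis for claims about effects. Define Cohen's d for the intervention effect as the between-group d. Report within-group changes from baseline to four months, and from baseline to 12 months in the intervention group, as means with confidence intervals and label them descriptive. State that a difference in significance between two within-group tests is not evidence of an effect. Repeat the 12-month caveat from the limitations in the Analyses section.

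The cost is wording. No data are lost, no further assessments are needed, and this point does not alter the sample size. The downside is that no formal 12-month effect claim can be made, which the design could not support in any case.

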## Background

Children who grow up in families with parental problems like for instance mental health or substance abuse problems, run an increased risk of developing a number of different physical and psychological health issues, as well as social problems (*e.g.*, [1-6]). Available figures indicate that this is widespread, affecting many children who experience one or more of these problems in their families. For instance, international estimates indicate that 12-39% of all children have parents with mental health problems [7-10]; 10-40% are affected by domestic violence [11-13]; 8-30% grow up with at least one problem drinking parent [14-17]; about 2% of US children have a parent in prison [18]. In Sweden, figures are similar, revealing that about 6% of all children aged 0–17 have at least one parent who has received inpatient psychiatric care [19], and approximately 20% have parents with alcohol problems [20,21], while about 30% of all children have divorced parents (http://www.scb.se) and approximately 2% have a parent in prison [22].

Support is available to these children *via* for instance the Child and Adolescent Psychiatric Care (BUP), the general school health care and the Social Services, who provide support through Family Centres (Familjecentraler), Contact Families (where children can spend weekends) [23] and in severe cases, foster care. Additionally, a relatively novel way to offer intervention programs to this target group is by the use of the Internet and there are currently a small number of internet-based controlled trials ongoing [24,25]. The most commonly offered intervention in Sweden to children in troubled families is support groups run by the Social Services and/or NGOs. Regardless of the underlying problem within the family, these support group interventions are all derived from the same fundamental psycho-educative manual-based intervention called Children are People Too (CAP) [26-28]. The support group interventions are aimed at strengthening children’s feeling of self-worth, their competencies and coping behaviour, and thereby to prevent a negative psycho-social development. Briefly, the groups provide information about the parent’s problems and children are able to share their experiences with other children during 8–15 weekly one and a half hour long meetings each addressing a special theme.

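### Treatment is given in support groups, but the sample size and the stated tests treat children as independent, so the 80% power is not supported and intervention-arm standard errors are too small if outcomes correlate within groups

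*Protocol article*

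**What the plan says.** **Delivery.** The Background section says that in the groups "children are able to share their experiences with other children", over 8–15 weekly meetings. The section on the interventions adds "various games, role plays and practices related to family problem and coping behaviour" and says the design varies somewhat with the programme or manual used. Contact between peers is therefore part of the treatment.

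**Control.** The control condition is a care-as-usual waiting list. Under Assessment, controls are offered the intervention only after the four-month follow-up. Under Strengths and limitations, that follow-up is the only time at which the arms can be compared.

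**Sample size.** The target effect is stated as "corresponding to a standardized mean difference of Cohen’s d >0.5". The method is described as "Based on differences between means, an *a priori* calculation of the estimated sample size, using the G*Power software", with an allocation ratio of 1.8. The stated requirement reads: "a minimum of 116 participants (75 in the intervention group and 41 in the control group) enrol in the trial". The settings behind this figure are given as "power = 0.80, α = 0.05, one tailed". No ICC, group size or design effect appears.

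**Analysis.** The main analyses compare means between and within groups at baseline and follow-up. The choice of test rests on normality alone: "Analyses include either parametric or non-parametric tests, depending on whether or not the various outcome data are normally distributed". The article does not mention clustering anywhere.

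**The concern.** Children in one support group share leaders, a manual, the same peers and the same sessions. Their outcomes at four months may be more alike than those of children from different groups. At the between-arm comparison only the intervention arm is nested in treatment groups, which makes this a partially nested design. If the correlation is ignored, the variance of the intervention mean is understated, intervals are too narrow, p-values are too small and the quoted power is too high. Because the test is one-tailed in favour of the intervention, the excess error all goes towards declaring benefit.

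The within-group comparisons are more exposed. In the intervention arm they lie wholly in the clustered data, and at 12 months they are the only comparison available.

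**Working it through.** **Inputs from the article (Sample size):** n = 75 intervention and 41 control, d = 0.5 with SD 1, one-sided α = 0.05, target power 0.80, ratio 1.8.

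**Assumptions, because the article gives no values:** m enrolled children per support group; ICC within groups in the intervention arm; total variance 1 in both arms; controls uncorrelated.

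**1. The plan's own figure.**
- Naive variance = 1/75 + 1/41 = 0.01333 + 0.02439 = 0.03772, so SE = 0.1942 and d/SE = 2.574.
- The one-sided t-test on 114 df then has power 0.820. At ratio 1.8 a t-test needs only about 109–110 children for 80%.
- A Wilcoxon–Mann–Whitney calculation (efficiency 3/π, normal data) needs 114.2 before rounding and gives power 0.804 at 75/41.
- The stated 116 is thus recovered as a calculation on independent children, that is, with a design effect of 1. On the t-test basis it carries a little slack.

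**2. Clustering in the intervention arm only.**
- Design effect: DE = 1 + (m − 1) × ICC.
- Variance = DE/75 + 1/41.
- True one-sided error of the naive test = 1 − Φ(1.645 × naive SE / true SE).
- Power: noncentral t with Satterthwaite df, using 75/m groups.

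Example, m = 8 and ICC = 0.10: DE = 1 + 7 × 0.10 = 1.70. Variance = 1.70/75 + 1/41 = 0.02267 + 0.02439 = 0.04706, so SE = 0.2169. The ratio to the naive SE is 1.117. True error = 1 − Φ(1.645/1.117) = 0.070. With d/SE = 2.305 on about 29 df, power is 0.728.

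| Enrolled per group | ICC | DE | True SE / naive SE | One-sided error | Power |
|---|---|---|---|---|---|
| independent | 0 | 1.00 | 1.000 | 0.050 | 0.820 |
| 3 | 0.02 | 1.04 | 1.007 | 0.051 | 0.812 |
| 3 | 0.05 | 1.10 | 1.018 | 0.053 | 0.805 |
| 3 | 0.10 | 1.20 | 1.035 | 0.056 | 0.793 |
| 6 | 0.02 | 1.10 | 1.018 | 0.053 | 0.802 |
| 6 | 0.05 | 1.25 | 1.043 | 0.057 | 0.783 |
| 6 | 0.10 | 1.50 | 1.085 | 0.065 | 0.754 |
| 8 | 0.02 | 1.14 | 1.024 | 0.054 | 0.794 |
| 8 | 0.05 | 1.35 | 1.060 | 0.060 | 0.769 |
| 8 | 0.10 | 1.70 | 1.117 | 0.070 | 0.728 |
| 8 | 0.20 | 2.40 | 1.223 | 0.089 | 0.655 |

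The Satterthwaite df run from about 64 (3 per group) to about 29 (8 per group, ICC 0.10), and to about 23 at 8 per group and ICC 0.20.

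**3. Within-group comparisons in the intervention arm.** No control arm dilutes the design effect, so true SE / naive SE = √DE. If the same ICCs applied to change scores (a further assumption), the ratio is √1.25 = 1.12 at 6 per group and ICC 0.05, and √1.70 = 1.30 at 8 per group and ICC 0.10. A nominal two-sided 5% test then has error 2 × [1 − Φ(1.96/1.12)] ≈ 0.08 and 2 × [1 − Φ(1.96/1.30)] ≈ 0.13.

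**The case against.** **Power may still be about 80%.** A reader might infer that the stated power is definitely missed. The article does not support that, since it gives neither ICC nor group size. What drives the design effect is the number of *enrolled* children per group, and that may be well below attendance: enrolment needs an individual application, signed consent and no earlier support group, and the article reports recruitment difficulties. With 3 per group and ICC 0.05, or 6 per group and ICC 0.02, power stays at 0.80 or just above. This objection stands. The 80% is unsupported rather than shown to be wrong.

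**The merging sentence.** A reader might take "all data will be merged and thus treated equally, irrespective of the nature of the support group" to say that the group attended will be ignored. It does not: the bracket that follows defines nature as the type of parental problem, and the sentence rules out analysis by problem type. It is no evidence on whether the particular group is modelled. The differences by group belonging conceded under Strengths and limitations likewise concern problem type.

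**The model may be specified elsewhere.** The article names no particular test, and model details are commonly left to an analysis plan, which is not shown. This weakens the analysis half of the point but not the sample-size half: that calculation is fully stated and assumes independence. The Analyses text also chooses between tests on normality alone, which leaves no place for the group.

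**Controls may share sites with treated children.** Under Allocation, the vast majority of controls come from the support groups' own waiting lists. Correlation shared across arms could offset part of the inflation. The article does not allow this to be quantified, and the variance formula above ignores it.

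**Conclusion.** The point holds in a limited form. The sample size and the stated tests treat children as independent although one arm is treated in groups. For any positive within-group correlation the intervention-arm standard error is understated, and the 80% power is not supported.

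For 3 to 8 enrolled children per group and ICC 0.02 to 0.10, power is about 0.73–0.81 against 0.82 under independence, and the one-sided error is about 5.1–7.0%. A harder case of 8 per group and ICC 0.20 gives 0.66 and 8.9%. The effect on within-group comparisons is larger.

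All of these figures rest on assumed group sizes and ICCs, equal total variances and no correlation shared across arms. Over the central range the effect on the between-arm comparison is modest. It should be fixed, but it does not undermine the trial by itself. Confidence is moderate because the two quantities that set its size are not given.

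**What to change.** 1. **Data.** Record the support group attended for every intervention child, together with the site or waiting list for every child. This needs doing during collection, because it may not be recoverable later.
2. **Analyses.** State that the comparisons allow for clustering by support group in the intervention arm. One suitable choice is a partially nested mixed model with a random intercept for support group in that arm and Satterthwaite or Kenward–Roger degrees of freedom. If controls come from the same sites, add site or waiting list as a term shared by both arms. Apply the same allowance to the within-group comparisons, including those at 12 months.
3. **Sample size.** Restate the power of 75/41 for a stated number of enrolled children per group and a stated ICC, preferably as a short range, in place of the single 0.80.

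**Cost.** One or two identifier variables and revised wording, with no additional children. Intervals become slightly wider and the stated power less favourable.
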